### Qualitative analysis

In all, 40 interviews will be carried out by a researcher blind to participant treatment allocation.

Audio-recordings of the 40 interviews will be transcribed verbatim, anonymised and imported into analysis software QRS NVivo. The researcher will conduct primary coding of the narrative data and the five stages of framework analysis as described by Ritchie and Lewis^44^ will be followed: familiarisation, identifying a thematic framework, indexing, charting and mapping/ interpretation.

Using a thematic approach,^45^ data will be inductively coded, codes grouped to create categories and a descriptive account will be produced. Up to 10 interviews will be double coded to increase the validity of the findings. Double coding means more than one researcher independently assigning pre-specified codes to the qualitative data. NVivo software (QSR International) will be used to facilitate the double coding process. This allows for coding comparisons to be run between different coders. The results are returned according to the kappa coefficient score and the percentage of agreement between coders. After double coding transcripts, we plan to use this coding comparison for discussion and reflection on the data. The numeric measure will be used as a method of comparison to gauge if there is agreement and understanding of the definitions of the codes between team members. Any discrepancies identified will then be discussed until an agreement is reached and any differences resolved. The account will provide structured descriptions of participants’ experience of self-management and splints, including reasons for their views about effectiveness as well as information about acceptability and adherence.

### Quality of life analysis

The EuroQol 5 Dimensions 5-Levels (EQ-5D-5L) questionnaire^46^ will be administered to participants at baseline, 8 weeks and 12 weeks. Responses will be converted into utilities using tariffs estimated from a representative sample of the UK population.^47^ Survival information collected from the trial will be combined with EQ-5D utilities to generate Quality Adjusted Life-Years (QALYs).

### Economic evaluation and analysis

The perspective adopted in the economic analysis will be that of the NHS. Costs associated with the following healthcare resource categories over the 8-week intervention period and follow-up period (12 weeks) will be included.

Intervention provision (including splints and clinical staff time required for splinting); andPrimary care contacts, including surgery and home visits by GPs, nurses, and out-of-hours medical services, and community therapists; andHospital care services, including scheduled and unscheduled inpatient admissions, surgery, accident and emergency visits and outpatient care contacts.

Primary and hospital care resource use will be obtained from patient questionnaires administered at 8 weeks and at 12-week follow-up. Healthcare resources will be valued using unit cost schedules such as Personal Social Services Research Unit and NHS Reference costs. Costs associated with splints and other disposables will be obtained from the manufacturers and the NHS Supply Chain catalogue. Using the Work Productivity and Activity Impairment Questionnaire,^48^ the number of work days lost by study participants and the impact that OA had on the levels of productivity/activity and unpaid work will also be measured over both study periods.

An economic evaluation adherent to guidelines for good economic evaluation practice^49^ will be undertaken. A within-trial cost-utility analysis will explore the incremental cost per QALY gained by splinting of the thumb base and a self-management programme when compared with (1) placebo-splinting and a self-management programme and (2) a self-management programme alone. The analyses will be conducted at 8 weeks and at 12 weeks. Cost and effect results will be reported as means with SD, with mean differences between the two patient groups reported alongside 95% CIs. Depending on the amount of missing cost and quality of life data, missing data will be imputed using recommended multiple imputation methods,^50^ with results from this analysis being presented as an additional sensitivity analysis.

Incremental cost-effectiveness will be calculated by dividing the difference in costs by the difference in effects. Uncertainty around the incremental cost-effectiveness ratio will be explored using non-parametric bootstrapping. A supplementary economic evaluation including non-NHS costs will be conducted in an additional sensitivity analysis. This will include costs of impaired productivity/activity and, any work and non-work days (eg, leisure or non-paid work) lost due to illness will be valued using mean average wages for those in employment. For participants who are retired or those not in employment, loss in activity levels (eg, leisure, caring or non-paid work activities) due to illness will be valued using minimum wages.

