## Introduction

Osteoarthritis (OA) is a leading cause of pain, disability, healthcare utilisation and productivity loss in the UK. Each year approximately two million adults visit their general practitioner (GP) with symptoms of OA.^1^ OA is more prevalent in women, the incidence increases with age and recent estimates suggest more than 150 million Europeans have radiographic hand OA and 15 million have symptomatic arthritis.^2^ Symptomatic thumb base (first carpometacarpal and/or scaphotrapezial joint) OA affects approximately 22% of people aged 50 years and over.^3^ Thumb base OA is likely to become more prevalent in the future since the incidence increases with age^4^ and is identified as a priority for treatment as it causes more pain and disability and is associated with a worse prognosis than other hand sites affected by OA.^5^

Patients with thumb base OA present with predominantly mechanical usage-related pain over the thumb base^6^ and are more likely to have more pain, work disability and reduction in quality of life and function, and to receive more anti-inflammatory drugs and more splinting than participants with OA affecting other hand joints^5 7–9^

Thumb base OA affects entire hand function^10^ and the overall impact, particularly in older people, can be substantial, with many experiencing difficulties with daily household, caring, work and leisure activities.^11^ Despite the scale of this problem, it appears that both patients and practitioners often believe that there is little that can be done.^12^

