**Exclusion criteria**	
**1**	Consultation with therapy department or treatment for this thumb problem (excluding pain killers and anti-inflammatories) in the previous 6 months
**2**	Intra-articular joint injection to wrist, fingers or thumb in the previous 2 months
**3**	Fractures or significant injury or surgery to the wrist or hand within the previous 6 months
**4**	Red flags. History of serious illness or disease such as any other diagnosed rheumatic conditions: gout, psoriatic arthritis, ankylosing spondylitis, connective tissue disorders (systemic lupus, systemic sclerosis), resulting in inflammatory arthritis in the hand/s, or, progressive neurological signs, or acute swollen hand joint
**5**	Diagnosis of dementia or other significant disorder likely to affect communication
**6**	Already received thumb splints for thumb base OA
**7**	Skin disease that may interfere or contraindicate splint wear
**8**	Participant of a drug or medical device trial in the last 12 weeks

CMCJ, carpometacarpal joint; OA, osteoarthritis; OTTER Trial, Osteoarthritis of the Thumb Therapy Trial.

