### Concomitant care

Any relevant contralateral thumb treatment for participants will be delayed until the end of the trial. There will be no alteration in participants’ general concomitant care while on the trial. Additional treatments, for example, joint injection, surgery and reported purchase or use of own splints during the study period will be captured on self-report questionnaires. Criteria for modifying allocated interventions are detailed within the OTTER II Trial Safety Information.

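### The NHS-perspective cost list has no category for prescribed medicines, so any between-arm difference in prescribed analgesics or anti-inflammatories drops out of the incremental cost

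*Protocol article*

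**What the plan says.** The section Economic evaluation and analysis states the viewpoint: "The perspective adopted in the economic analysis will be that of the NHS". It then sets the scope: "Costs associated with the following healthcare resource categories over the 8-week intervention period and follow-up period (12 weeks) will be included". The list has three entries. The first is provision of the intervention, meaning splints and the staff time for splinting. The second is contacts with primary care. The third is hospital care, from admissions to outpatient contacts. Medicines appear in none of the three. Price sources for healthcare resources are given as examples, and no drug price source is among them. The supplementary non-NHS analysis describes lost productivity and activity and does not mention bought medicines.

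Three other places bear on whether drug use is to be expected:

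- Table 1, exclusion criterion 1, rules out "Consultation with therapy department or treatment for this thumb problem (excluding pain killers and anti-inflammatories) in the previous 6 months", so drug use for the thumb does not bar entry.
- Concomitant care says: "There will be no alteration in participants’ general concomitant care while on the trial".
- The Introduction says that patients with thumb base OA are more likely "to receive more anti-inflammatory drugs and more splinting than participants with OA affecting other hand joints".

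Table 3 schedules a health utilisation questionnaire at 8 and 12 weeks. Its items are not shown.

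**The concern.** A cost-utility analysis from the NHS viewpoint should count the NHS costs that the compared treatments could plausibly change. The trial tests a device meant to relieve pain, in people whom the article itself describes as users of anti-inflammatory drugs, and drug use is left free. Prescribed medication is therefore a cost that could differ by arm, and the cost list has no place for it.

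The analysis forms the ICER as the difference in cost over the difference in effect. A cost left out of every arm is harmless only if it is equal across arms. If it differs, the whole difference is lost from the numerator. The follow-up is short, so the QALY difference in the denominator will be small, and a modest sum per patient can move the ratio noticeably. This affects both planned comparisons: verum splint against placebo splint, and verum splint against self-management alone.

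**Working it through.** **No plan figure to reproduce.** The article gives no cost, drug-use rate or QALY difference. The check is first one of text, then of how the omission carries through the formula.

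**Step 1: does any category hold prescribed medicines?**

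| Category in the article | What it covers | Prescribed medicines? |
|---|---|---|
| Intervention provision | Splints, staff time | No |
| Primary care | Contacts: GP, nurse, out-of-hours, community therapist | No; a prescription is not a contact |
| Hospital care | Admissions, surgery, emergency visits, outpatient contacts | Not named; drugs prescribed in the community are not a hospital service |

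The list of categories is not introduced as a set of examples. The article does use that device elsewhere, for co-treatments and for unit cost schedules.

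**Step 2: how the omission enters the ICER.** Let ΔC be the incremental cost over the listed categories, ΔD the incremental cost of prescribed medication (verum minus comparator), and ΔQ the incremental QALYs.

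- ICER on the article's list = ΔC / ΔQ
- ICER with prescribed medication = (ΔC + ΔD) / ΔQ
- Error = −ΔD / ΔQ

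The error is zero only when ΔD = 0. Its sign is that of −ΔD/ΔQ. For a positive ΔQ, the list overstates the ICER when verum patients use less prescribed medication and understates it when they use more.

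**Step 3: illustration. All inputs are assumptions.** Take ΔC = £50 and ΔQ = 0.002 or 0.005. Over 12 weeks (12/52 = 0.231 years) those gains correspond to constant mean utility differences of 0.002/0.231 = 0.009 and 0.005/0.231 = 0.022.

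| ΔD | ICER at ΔQ = 0.002 | ICER at ΔQ = 0.005 |
|---|---|---|
| −£20 | 30/0.002 = £15,000 | 30/0.005 = £6,000 |
| −£10 | 40/0.002 = £20,000 | 40/0.005 = £8,000 |
| −£5 | 45/0.002 = £22,500 | 45/0.005 = £9,000 |
| £0 (the list as written) | 50/0.002 = £25,000 | 50/0.005 = £10,000 |
| +£10 | 60/0.002 = £30,000 | 60/0.005 = £12,000 |

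Each omitted £1 is worth 1/0.002 = £500 or 1/0.005 = £200 per QALY. The table shows sensitivity. It does not estimate what will happen in this trial.

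**The case against.** **The list may not be exhaustive.** The article says that the named costs will be included, not that all others are excluded. It promises to follow good-practice guidance for economic evaluation, and a fuller costing specification may exist. That is fair, and it keeps the point modest. It does not remove it: the article chose to define the scope, defined it without an open-ended qualifier, and the definition is narrower than the stated viewpoint.

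**The omitted cost may be small.** Only NHS-prescribed drugs belong in the base case, since bought ones lie outside the NHS viewpoint, and the horizon is 12 weeks. This stands. The documents do not settle it either way.

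Three stronger readings are tempting and not supported.

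- *Analgesic use is not recorded.* A reader might infer this because the named co-treatments are injection, surgery and own splints. But the wording is "Additional treatments, for example, joint injection, surgery and reported purchase or use of own splints during the study period will be captured on self-report questionnaires", which gives examples only, and the items of the health utilisation questionnaire are not shown. Non-collection is not established.
- *Analgesic substitution masks the effect on the primary outcome.* The trial is described as pragmatic, the main analysis is by intention to treat, and usual care is deliberately unaltered in all arms. Medication taken after randomisation is then part of the effect being estimated. The documents also give no rate of use from which an attenuation could be worked out.
- *Drug savings are the main offset, so the splint's value is understated.* No figure supports the ranking. The direction holds only if verum patients use fewer prescribed drugs. The Introduction compares thumb base OA with OA in other hand joints and says nothing about differences between randomised arms.

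**Conclusion.** The point holds for the cost scope and no further. As written, the NHS-perspective analysis has no category for prescribed analgesics and anti-inflammatories, although the article shows that their use is permitted and to be expected. Any between-arm difference in that cost would be absent from the incremental cost and from the ICER.

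Size and direction cannot be derived from the documents. Under the assumed QALY gains of 0.002 to 0.005, the ICER moves by £500 to £200 per QALY for each £1 of omitted difference, upward or downward. If prescribed use turns out equal across arms, the ICER is unaffected. The primary outcome analysis and the sample size are not in question.

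**What to change.** In Economic evaluation and analysis, add prescribed medication as a further NHS cost category and name a drug price source, or state why it is left out. Take use from the health utilisation questionnaire at 8 and 12 weeks. If that questionnaire has no medication item, add a short one that separates prescribed from bought drugs. Put bought analgesics into the supplementary non-NHS analysis. Report medication use by arm descriptively.

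The cost is one extra cost line and, at most, one short questionnaire item with a little added burden for participants. Nothing about participants' treatment changes.

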**Methods and analysis:**

Participants aged 30 years and over with symptomatic thumb base OA will be recruited into the trial from secondary care occupational therapy and physiotherapy centres. Following informed consent, participants will complete a baseline questionnaire and then be randomised into one of three treatment arms: a self-management programme, a self-management programme plus a verum thumb splint or a self-management programme plus a placebo thumb splint. The primary outcome is the Australian Canadian Osteoarthritis Hand Index (AUSCAN) hand pain scale. The study endpoint is 8 weeks after baseline. Baseline assessments will be carried out prior to randomisation and outcomes collected at 4, 8 and 12 weeks. Cost-effectiveness analysis will be conducted and individual qualitative interviews conducted with up to 40 participants after 8 weeks to explore perceptions and outcome expectations of verum and placebo splints and exercise.

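### The economic section states no adjustment of QALY differences for baseline EQ-5D, which leaves the estimate needlessly imprecise and exposed to chance imbalance

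*Protocol article*

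**What the plan says.** Under Quality of life analysis in the protocol article, the EQ-5D-5L "will be administered to participants at baseline, 8 weeks and 12 weeks". Responses are converted to utilities and combined with survival information to give QALYs. No interpolation rule is given. The Abstract confirms the order of events: "Baseline assessments will be carried out prior to randomisation and outcomes collected at 4, 8 and 12 weeks".

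Under Economic evaluation and analysis, the verum splint arm (B) is compared with the placebo splint arm (C) and with self-management alone (A). On timing: "The analyses will be conducted at 8 weeks and at 12 weeks". On the estimate, costs and effects are given as means with SD, and "mean differences between the two patient groups reported alongside 95% CIs". On the ratio: "Incremental cost-effectiveness will be calculated by dividing the difference in costs by the difference in effects". On its uncertainty: "Uncertainty around the incremental cost-effectiveness ratio will be explored using non-parametric bootstrapping". No covariate or regression model is named.

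Two other sections bear on this. Under Randomisation, the minimisation factors are centre, baseline AUSCAN pain category and treated hand dominance; EQ-5D is not among them. Under Statistical analysis, AUSCAN pain is analysed by ANCOVA with baseline pain and the stratification factors, and continuous secondary outcomes are handled similarly. Nothing there mentions QALYs or costs.

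**The concern.** A QALY over 8 or 12 weeks, built from a baseline and one or two later measurements, contains a large share of utility measured before treatment began. That share carries no information about the treatment. If the incremental QALY is a plain difference in arm means, any chance difference in baseline utility enters it twice: directly through the baseline term, and indirectly because later scores correlate with baseline.

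Over so short a horizon the QALY gain to be detected is only a few thousandths. The ICER divides by that small number, so noise of the same size can change its magnitude or sign. The baseline value that would remove much of this noise is already on the questionnaire, and the clinical analysis uses its own baseline in just this way.

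**Working it through.** **Inputs from the article.** EQ-5D at weeks 0, 8 and 12; horizons of 8 and 12 weeks; 92 evaluable participants per arm. The last figure reproduces: a three-group F test with one arm 0.4 SD from the other two needs 92 per arm (power 80.3%), and 92/0.80 = 115, × 3 = 345. The article gives no QALY figure to reproduce.

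**Assumptions, not in the article.** Linear interpolation between measurements; the same utility SD σ at each time point, 0.20 with a range of 0.15 to 0.25; the same correlation r between any two time points, 0.5 to 0.7.

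**1. Weight of baseline.** With U0, U8 and U12 the utilities and time in weeks:
- 8-week QALY = (4·U0 + 4·U8)/52, so the baseline share is 4/8 = 1/2.
- 12-week QALY = (4·U0 + 6·U8 + 2·U12)/52, so the baseline share is 4/12 = 1/3.

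**2. Variance removed by adjusting for U0.** This is the squared correlation of the QALY with U0, and σ cancels.
- 8 weeks: (4+4r)²/(32+32r) = (1+r)/2, giving 0.75 at r = 0.5 and 0.85 at r = 0.7.
- 12 weeks: (4+8r)²/(56+88r), giving 64/100 = 0.64 at r = 0.5 and 92.16/117.6 = 0.78 at r = 0.7.

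**3. Standard error of a two-arm QALY difference (σ = 0.20, 92 per arm).**

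| Horizon | r | Unadjusted | Adjusted |
|---|---|---|---|
| 8 weeks | 0.5 | 0.0039 | 0.0020 |
| 8 weeks | 0.7 | 0.0042 | 0.0016 |
| 12 weeks | 0.5 | 0.0057 | 0.0034 |
| 12 weeks | 0.7 | 0.0062 | 0.0029 |

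**4. Effect of an ordinary imbalance.** One standard error of the baseline difference is 0.20 × √(2/92) = 0.029.
- Direct part, either horizon: 0.029 × 4/52 ≈ 0.0023 QALY.
- With carry-over into later scores, 8 weeks: 0.029 × (4+4r)/52 ≈ 0.0034 to 0.0039.
- With carry-over, 12 weeks: 0.029 × (4+8r)/52 ≈ 0.0045 to 0.0054. For σ from 0.15 to 0.25 the range widens to 0.0034 to 0.0068.

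**5. Yardstick.** Take an illustrative utility gain of 0.03 at weeks 8 and 12 from a shared baseline. Under the same interpolation it yields 0.03 × 4/52 = 0.0023 QALY at 8 weeks and 0.03 × (6+2)/52 = 0.0046 at 12 weeks. Multiplying 0.03 by the full 12/52 would give 0.0069, but that supposes the benefit is present from day 0, which conflicts with the interpolation rule.

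**The case against.** The strongest reply is that the article does not prescribe an unadjusted analysis. A reader might infer that raw differences are planned, but the text never says so. A regression-adjusted contrast is also a mean difference with a confidence interval, the definition of the ICER holds for adjusted increments, and a bootstrap can wrap a regression. The article is condensed, defers full detail to a statistical analysis plan, and promises to follow good-practice guidelines for economic evaluation. This stands: the point cannot be put as a plan to use raw differences. What remains is that the section does state how the incremental effect is summarised, and that description, taken literally, is the unadjusted difference. The ANCOVA wording belongs to the clinical outcomes and is not carried over.

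A reader might also infer bias. That is not supported. Baseline precedes randomisation, so the unadjusted difference is right on average, and its interval and bootstrap would carry the extra variance. The loss is in precision, and in error conditional on the imbalance that actually occurs.

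A third tempting reading is that the reference to two patient groups overlooks the third arm. The same paragraph sets out pairwise comparisons, and each has two groups, so the phrase reads naturally that way.

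Finally, the QALY sizes rest on assumed inputs, and about half or less of the shift in step 4 (0.0023 of 0.0045 to 0.0054) comes from the baseline weight itself; the rest is carry-over. Minimising on pain category may also make large utility imbalances somewhat less likely, by an amount the article does not allow one to calculate.

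**Conclusion.** The concern holds in a limited form. The economic section describes an estimator for incremental QALYs and states no baseline EQ-5D adjustment, although the covariate is collected before randomisation and is not balanced by design. Used unadjusted, the estimator is valid but inefficient.

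The variance reduction depends on linear interpolation and an equal correlation of 0.5 to 0.7, but not on the SD. The absolute shift depends also on the assumed SD of 0.20 and 92 per arm. On those terms, an unremarkable imbalance is about as large as the QALY yield of a 0.03 utility gain at 12 weeks, and larger than it at 8 weeks. The primary clinical analysis is unaffected.

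**What to change.** State the QALY interpolation rule. Estimate incremental QALYs for B versus A and B versus C by regression on arm, baseline EQ-5D utility and the minimisation factors. Refit that model in each bootstrap sample, and make it the base case for the ICER. Keep the unadjusted means with SD as descriptive results. If the full protocol or a health economics plan already says this, a one-line reference to it is enough.

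The cost is a few sentences in the economic section and a few lines of code. No new data, visits or participants are needed.
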